### Data monitoring

A Data and Safety Monitoring Committee (DSMC) will perform a safety interim analysis when 7000 of the 14,000 patients have been randomised. In the safety analysis, the two PEWS models will be compared in terms of transfers to the PICU or transfers from regional hospitals to the university hospital. An independent statistician will perform the analysis and provide the results to the DSMC. To give recommendations on whether the trial should terminate or continue, the DSMC will use the Haybittle-Peto statistical approach as a guide [15]. The final decision regarding termination or continuation of the trial will be made by the research group, which consists of the principal investigator and three other members. Depending on the recommendations of the DSMC, further safety analyses could be performed. The safety analysis has been performed, and the DSMC had no comments.

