### Hypothesis

The hypothesis is that the Central Denmark Region PEWS is superior to the Bedside PEWS in terms of reducing hospitalised children’s unplanned transfers to the intensive care unit and transfers from regional hospitals to the university hospital due to clinical deterioration requiring proximity to a paediatric intensive care unit (PICU).

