### Outcomes

The primary outcome is the sum of unplanned transfers to the PICU and transfers from regional hospitals to the university hospital or the number of deaths. Transfers from regional hospitals to the paediatric department at the university hospital are equated with transfers to the PICU; children who need intensive care at the regional hospitals will be transferred to the paediatric department at the university hospital to ensure proximity to the PICU.

The secondary outcomes are as follows:Paediatric Index of Mortality scoreSeverity of illness during PICU stay based on invasive ventilation and inotropesLength of hospital stayLength of PICU stay

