### Sample size

A power calculation was made based on accessible data from 2013 from the departments that are currently employing PEWS models. The available preliminary data showed 154 unplanned transfers to the PICU out of 10,000 admissions. With a power of 80%, a 5% significance level and an expected 30% reduction in the number of transfers to intensive care, we would have to include 7112 children in each group. The total available study population is 26,800 children annually.

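### The stated safety comparison counts transfers but not deaths, so a child who deteriorates unrecognised and dies without transfer is a non-event in it

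*Protocol article*

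**What the plan says.** The Data monitoring section of the protocol article plans a "safety interim analysis when 7000 of the 14,000 patients have been randomised". It states the content of that look: "the two PEWS models will be compared in terms of transfers to the PICU or transfers from regional hospitals to the university hospital". The Haybittle-Peto approach is to guide the committee, and no boundary value is given. The section reports that the look has taken place and that the committee raised nothing. It leaves later looks open: "Depending on the recommendations of the DSMC, further safety analyses could be performed".

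The Outcomes section defines the primary outcome more widely. After unplanned PICU transfers it adds "transfers from regional hospitals to the university hospital or the number of deaths".

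The outcome data listed under Data collection and management are transfers and the two lengths of stay. Death is not among them. The regression described under Statistical methods takes unplanned PICU admission as its outcome. The Hypothesis section treats fewer transfers as the benefit: the regional model is to be "superior to the Bedside PEWS in terms of reducing hospitalised children’s unplanned transfers to the intensive care unit".

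**The concern.** Both scores drive an action algorithm that decides who is seen, how soon and by whom. Transfer is therefore partly a product of the score under test as well as a consequence of the child's illness. A low transfer count can mean that deterioration was averted, or that it was not recognised and the child never reached intensive care. A safety comparison should be able to tell these apart, and deaths are the component of the trial's own primary outcome that would help most.

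The other listed outcomes do not fill the gap. The PIM3 score, ventilation, inotropes and length of PICU stay exist only for children who reach the PICU. Length of hospital stay covers everyone, but a death on the ward ends the stay and may shorten it.

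At stake is what may be concluded about safety. The abstract's discussion already says that the study demonstrates the new model's safety, and the Data monitoring section reports a look without comments.

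**Working it through.** The plan gives no figure for this point and no death rate. The check therefore has a textual part and an illustration.

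**1. The sections side by side**

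| Section | Transfers | Deaths |
|---|---|---|
| Outcomes (primary) | yes | yes |
| Data collection and management (outcome data) | yes | not listed |
| Statistical methods (primary model) | PICU admissions | not named |
| Data monitoring (safety comparison) | yes | not named |

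**2. How each course of a deteriorating child is counted**

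| Course | Stated safety comparison | Outcomes section |
|---|---|---|
| Recognised, transfer averted | non-event | non-event |
| Recognised, transferred | event | event |
| Missed, transferred late | event | event |
| Missed, recovers without transfer | non-event | non-event |
| Missed, dies without transfer | non-event | event |

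The first and last rows cannot be told apart in the safety comparison. They differ under the Outcomes definition.

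**3. Inputs for the illustration**

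- Children per arm at the look: 7000 / 2 = 3500 (Data monitoring; 1:1 ratio from Allocation).
- Event rate: "154 unplanned transfers to the PICU out of 10,000 admissions", so 154 / 10,000 = 1.54% (Sample size). This covers PICU transfers only.
- Planned effect: a 30% relative reduction (Sample size).
- Assumed, not in the documents: both arms have the same number of deteriorating children; one model misses 30% of them; the other misses none and has no deaths.

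**4. Transfers**

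- Expected per arm: 3500 × 0.0154 = 53.9, about 54.
- Under the planned benefit: 53.9 × 0.7 = 37.7.
- Under the assumed 30% miss with no later transfer: 54 × 0.3 = 16.2, about 16 missed, leaving 54 − 16 = 38.
- Test of 54 against 38 (Pearson, no continuity correction): pooled rate 92 / 7000 = 0.01314; SE = √(0.01314 × 0.98686 × 2 / 3500) = 0.00272; z = (16 / 3500) / 0.00272 = 1.68; p = 0.093.

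On transfers alone, 38 from missed children looks the same as 37.7 from real benefit.

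**5. Deaths among the 16 missed children (range, all assumed)**

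| Deaths | Transfers | Transfers plus deaths | p, combined | Deaths alone | Fisher p |
|---|---|---|---|---|---|
| 0 | 54 v 38 | 54 v 38 | 0.093 | 0 v 0 | 1.0 |
| 2 | 54 v 38 | 54 v 40 | 0.15 | 0 v 2 | 0.50 |
| 4 | 54 v 38 | 54 v 42 | 0.22 | 0 v 4 | 0.12 |
| 8 | 54 v 38 | 54 v 46 | 0.42 | 0 v 8 | 0.008 |
| 16 | 54 v 38 | 54 v 54 | 1.0 | 0 v 16 | 0.00003 |

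Adding deaths to the combined count removes the false advantage only gradually, and at most brings the arms level. The separate column of deaths is what shows the harm.

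**6. Sensitivity to late transfer and to the miss rate**

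- All 16 transferred late: 54 against 54, no false advantage.
- Half transferred late, no deaths: 38 + 8 = 46 against 54, p = 0.42.
- A 10% miss with no later transfer: 53.9 × 0.9 = 48.5 against 53.9. The bracketing counts of 48 and 50 against 54 give p = 0.55 and 0.69, so such a difference shows little either way.

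**The case against.** The strongest reply is that the trial's own reasoning points the other way. The Discussion expects early recognition to avert decompensation and the need for higher care, so poorer recognition should produce more transfers, and later ones. The Outcomes section also says that children who need intensive care at regional hospitals are transferred. This stands. A reader might infer that a model which misses deterioration would look safer, or that the measure runs backwards. The documents do not support that: only missed children who die or recover without transfer drop out of the count.

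A reader might also infer that the monitoring committee saw nothing on which missed deterioration could show as harm. That goes too far. Late transfers do show it, and the committee's reports and charter are not at hand. What can be said concerns the comparison as the article states it.

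The omission may be shorthand, since the Abstract, Objective and Hypothesis also describe the outcome without deaths. That explains how it may have arisen, but the sections still disagree, and a safety comparison is where the disagreement matters most.

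The Discussion notes that death is rare in this age group. That is a good reason not to make death the sole efficacy outcome. It is no reason to leave deaths out of a safety table, where a few in one arm would deserve review.

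Finally, the first look is done, and recruitment was expected to end in February or March 2017. This limits the remedy to any further committee analysis and the final report. By January 2017, 12,000 children had been randomised, which is 12,000 − 7000 = 5000 beyond the planned look.

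**Conclusion.** The point holds in a limited form. The stated safety comparison is narrower than the trial's own primary outcome, and it treats a death without transfer as a non-event. A model that misses such children could look no worse, or better. Transfers alone cannot fully separate prevented from missed deterioration, so the uneventful interim look supports safety only with respect to transfers.

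The size cannot be fixed from the documents. Under the assumed 30% miss at 3500 per arm, the apparent difference in transfers runs from none (all transferred late) to 54 against 38 (none transferred). A 10% miss gives a difference too small to read. These figures rest on the assumed miss rates, on equal numbers deteriorating in each arm, and on a baseline rate that covers PICU transfers only.

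**What to change.** Reconcile Outcomes, Data collection and management, and Data monitoring:

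- Add in-hospital death to the listed outcome data.
- Define the safety comparison as transfers and deaths by allocated model, shown separately and combined, with each child counted once in the combined figure.
- Apply this to any further committee analysis and to the final safety report, for all randomised children.
- Until then, describe the completed look as covering the transfer comparison that the article states.

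Ventilation and inotropes may be added as markers of late transfer, but they cannot reveal children who were never transferred.

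The cost is one table and a wording change, provided the electronic charts record in-hospital death, which the article does not say. The drawback is that deaths will be few, so the table is descriptive. No new stopping boundary is needed.

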### Ethics and dissemination

The interventions directly affecting hospitalised children will be the measurement of pulse, saturation and blood pressure. The measurements are non-invasive; they cause no pain and only slight discomfort (blood pressure) and are standard procedures for most acutely ill, hospitalised children. Thus, they are expected to raise no concerns among children and parents. It is important that patients’ experiences of anxiety, concern or irritation are addressed. It is therefore crucial for ward nursing staff to inform patients about the rationale of the PEWS while they are measuring vital parameters and for nursing staff to be able to explain in a professional and clear manner why the measurement is important. Several studies have shown that bedside observations of vital parameters and simple algorithms based on these observations can identify patients at risk of deteriorating [9, 11, 16, 17]. It is therefore unethical to neglect reacting to these findings and not to implement a new ward practice.

### Dissemination policy

The results, whether positive, negative or inconclusive, will be published in a peer-reviewed international journal.

## Discussion

National and international models for early warning systems in adults exist [2, 18]. Nevertheless, several international reports have shown that failure to identify the signs of critical illness and subsequent lack of appropriate action for patients developing acute and critical illness remain a problem [19, 20].

In a PEWS review, Chapman et al. [21] concluded that there is considerable variation in the purpose, contents and threshold of actions of published PEWS models as well as a lack of evidence of their validity, reliability and applicability. Reliability was investigated only in one study, and no studies reported on health professionals’ experiences of the applicability of PEWS. In a British study of PEWS, there was a large variation in the use of parameters; 46 different parameters were used, and more hospitals used PEWS models that were not validated or thoroughly investigated [22]. A Cochrane review found that this also applies to early warning systems for adults, and the review drew attention to the lack of randomised controlled trials (RCTs) [2]. The present RCT compares two different PEWS tools.

Several different indicators of deterioration were considered as outcome measures for this trial. Cardiopulmonary arrest was initially considered, but other studies [9, 10, 23, 24] found it difficult to demonstrate an effect because the event rate of in-hospital cardiac arrest or death was low in this age group. Other proxies for the measurement of clinical deterioration were explored. Code-blue events were also considered as an indicator for identifying children at risk of clinical deterioration, but Duncan et al. [9] have discussed the limited number of code-blue events in relation to the challenge of developing screening mechanisms to identify children at risk of deterioration. Unplanned transfer to an intensive care unit has been used as a proxy for the measurement of clinical deterioration. Tucker et al. [25] demonstrated a statistically significant association between the PEWS and transfer to the PICU. In a retrospective case control study, Zhai et al. [26] used transfers to the PICU to develop an electronic health record-based automated algorithm and compared its effectiveness with that of two PEWS tools. For the present study, transfer to the PICU was chosen as a surrogate marker for clinical deterioration.

In conclusion, the development and implementation of the PEWS may prevent acute decompensation and the need for a higher level of care. It will help with early recognition and intervention on children at risk of deteriorating. The PEWS is also expected to assist in increasing healthcare professionals’ skills and competencies. This study will add to the limited body of knowledge of PEWS systems. It is also expected to contribute to deriving a common PEWS model in Denmark. Finally, a PEWS model can help reduce healthcare costs for society, as an intensive care hospital bed is more expensive than a hospital bed at a general paediatric department.

### Trial status

Patient inclusion in the PEWS project began in November 2014. All departments have been enrolling patients since March 2015. As of September 2016, 11,000 patients have been randomised. Patient recruitment is expected to end in February 2017.

## Abbreviations

DSMC: Data and Safety Monitoring Committee
PEWS: Paediatric Early Warning Score
PICU: Paediatric intensive care unit
PIM3: Paediatric Index of Mortality
RCT: Randomised controlled trial
